### Ethics approval

2.10

This study has been approved by Comitato Etico Indipendente, Azienda Ospedaliero-Universitaria ‘Consorziale Policlinico’ on February 2023 (prot. n. 0023249|09/03/2023).

## Discussion

3

### Anticipated results

3.2

This will be the first study that tries to understand the complex relationships between diet, intestinal microbiota and human breath in patients affected by BD through an innovative approach based on AI methods (Golob et al., 2023; Novielli et al., 2023; Papoutsoglou et al., 2023). Such an understanding can represent a significant step forward toward the comprehension of pathogenetic mechanism at the basis of BD onset and the identification of microbial, metabolic and immunological factors and therapeutic biomarkers able to control treatment outcome and to better understand how the such a treatment can modify microbiome. In fact, intestinal dysbiosis has been linked to inflammatory diseases (Douzandeh-Mobarrez and Kariminik, 2019) and recent studies have demonstrated that therapeutic treatment in rare rheumatological diseases can modify subclinical intestinal inflammation and dysbiosis (Manasson et al., 2020), highlighting the bidirectional nature of this correspondence. Furthermore, this study will evaluate for the first time with multivariate models if microbiome and breath modulation through the diet can improve disease activity in patients with BD under treatment. This analysis could enable us to find valuable markers to identify responders and non responders, allowing treatment optimization and a personalized therapeutic approach. This study could be also useful to analyze diet effects on BD activation and/or remission. Going into details, network approach thought for this study is aimed to catch functional structure of dynamic processes happening between microbiome and human host, to identify the coexistence of different microorganisms, to trace relationships between microorganisms and to identify cohesive groups that play fundamental roles in maintaining functional relationships in the global network during the treatment. Identification and quantification of some of the topological properties of the network modules can provide important information on microbiome interactions and on their relationship with possible disorders and anomalies in inflammatory and pathological states. Specifically, co-occurrence patterns and identified polymicrobial interactions will be related with other clinical and phenotypical data to detect correlations between network functional and structural properties and biological and pathological profiles in different starting conditions. This integrative approach is completely innovative, since it will allow to highlight some connectivity patterns linked to inflammatory states, pathologies, etiological agents and even the organisms responsible for pathology transmission.

In our study protocol, we propose groundbreaking methodologies for personalized understanding of Behçet’s disease. One avenue of exploration involves the utilization of breath analysis to identify distinct Volatile Organic Compounds (VOCs) patterns in exhaled breath (Di Gilio et al., 2020a). By harnessing the capabilities of artificial intelligence algorithms, we aim to explore the nexus between microbiome and metabolome offering a non-invasive and efficient approach for Behçet’s disease management. Here, machine learning takes center stage, enabling us to unravel complex patterns within the oral microbiome. The goal is to uncover unique microbiome signatures associated with Behçet’s disease, laying the groundwork for a personalized medicine approach. This exploration promises not only a deeper understanding of the disease but also the potential for tailored interventions based on individualized oral microbiome and metabolome profiles (Bellando-Randone et al., 2021).

In the third facet of our study, we introduce the application of explainable artificial intelligence to analyze microbiome and volatilome data related. This innovative approach addresses the limitations of traditional machine learning methods, offering a clear and interpretable understanding of disease-associated microbiome and metabolome biomarkers. By incorporating local explanation embeddings and an unsupervised clustering method, we could anticipate the identification of distinct subgroups among subjects (Novielli et al., 2023). These perspectives open the door to personalized interventions, marking a significant stride toward a more nuanced and effective treatment paradigm for Behçet’s disease.

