The target of the proposed study is the Behçet Disease (BD), also known as Silk Road disease, a rare, complex and multi-systemic chronic vasculitis, characterized by mucocutaneous, articular, vascular and ocular lesions and also by central nervous system (CNS) symptoms. The most recurring signs of this disease are relapsing genital and oral aphthae (that can also spread in the whole digestive tract), ocular pathologies (>50% of cases), arthralgia and/or arthritis (45% of cases), venous system vasculitis and thrombosis. If thromboses occur in the arterial system, they usually involve pulmonary vessels. Neurological signs (neuro-BD) are frequent (>20%); they often occur 1–10 years after the first symptoms, and include headache, hemiparesis, behavior alterations and sphincter dysfunctions. Nowadays, BD etiology is still not clear and cannot be traced back to a single root cause: the overactivation of the innate immune system, typical of this disease, seems to be caused by an altered T-cells homeostasis, but it is common thought that also some components of the human microbiome can promote an abnormal adaptive immune response, in presence of a favorable genetic background (Rodrìguez-Carrio et al., 2021). In fact, several studies have linked BD to an intestinal or oral microbiota dysbiosis: in particular, a decrease in number of butyrate-producing bacteria, associated to a lower level of butyrate in fecal samples of patients has been noted (Consolandi et al., 2015). As concerning gut, butyrate is involved in regulatory T cells differentiation (Furusawa et al., 2013) and in the release inhibition of pro-inflammatory cytokines (Weng et al., 2007). Low production of butyrate in patients suffering from BD may cause both reduced T-reg responses and T-cells immune-pathological responses activation, as suggested by the prevalence of T helper cells Th1 and Th17 in patients affected by BD (Alpsoy, 2016). Influencing intestinal microbiota, with factors such as the diet, can have a role in correcting intestinal dysbiosis and in reducing the severity of BD active phases. The evidence collected in the last decade highlight that adhering to dietary patterns which include high content of fibers can be linked to a better intestinal microbiota equilibrium; such a condition is favorable for short chain fatty acid (SCFA) producer bacteria and unfavorable for bacteria species associated to a pro-inflammatory pattern (Fu et al., 2020). Microbiota associated with dietary patterns rich in fibers was found to be positively correlated with high levels of SCFA (acetate, propionate, butyrate). Intestinal microbiota produces SCFA during indigestible polysaccharides (fibers) fermentation; these acid compounds have a well-documented protective role against several pathologies (Ho et al., 2018). To the best of our knowledge, a well-defined diet plan for BD does not exist, and the general advice is to follow a balanced diet and to maintain an ideal weight. Nevertheless, the just mentioned studies allow us to speculate that following a diet rich in fiber can correct intestinal dysbiosis, which is involved in the BD pathogenetic mechanism, and stimulate butyrate endogenous production from intestinal microbiota, bringing to a potential improvement of clinical manifestations.

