
Keeping all these evidence in mind, the proposed study is aimed to: (i) establish correlations between oral and intestinal microbiota, fecal and salivary volatilome, breath and phenotypic features of human hosts, affected by BD, active and/or in remission; (ii) identify, through cluster analysis methods of metabolites, different groups of patients affected by BD; (iii) identify some taxonomic units of oral and fecal microbiota and metabolic markers that majorly contribute to the prediction of different clinical outcomes (e.g., number of active mucosal lesions, remission following the Behçet Disease Current Activity Form (BDCAF)); (iv) identify, with XAI methods (Bellantuono et al., 2022), some personalized metabolic markers that, for each patient, contribute to the prediction of his/her clinical outcome (personalized medicine); (v) evaluate the effects of soluble fiber intake (inulin) on eubiosis/dysbiosis conditions of oral and intestinal microbiota and on endogenous production of butyrate; and (vi) establish correlations between eating habits and clinical outcome of patients.

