### Study design

2.1

The project we are going to propose will be performed in three different sub-activities. The first sub-activity includes a two-arm randomized study (duration: 3 months): patients in the control arm will keep on assuming the standard therapy while patients in the treatment arm will assume soluble inulin-type fructans (inulin 90% from *Cichorium intybus L.*; Farmalabor S.r.l., Canosa di Puglia, Italy), along with the standard therapy. At the starting of study and 3 months later, for each patient, the following samples and data will be collected:

samples for the assessment of oral/fecal microbiota;breath samples;clinical data such as Body Mass Index (BMI), disease duration, clinical phenotype and ocular, articular or mucocutaneous involvement;laboratory data such as Erythrocyte Sedimentation Rate (ESR) and C-reactive protein (CRP);information on breath components;information about eating habits, inviting patients to keep a food diary that can provide detailed descriptions on type and quantity of food and beverages consumed.

Furthermore, the second sub-activity will consist of:

analysis of volatilome in breath samples and microbiota in saliva and fecal samples;analysis of bacterial community taxonomic composition in fecal and saliva samples;chemical characterization of breath samples.

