### Interventional method

2.3

The fiber dietary supplement will be administered randomly to half of the study patients, in open-label mode. The BD patients will receive either inulin supplementation or placebo. The participants were recommended to consume the powder during the breakfast by mixing it to 150 mL of warm water and then stirring up the powder until dissolved.

At the starting point and 3 months later, for each BD patients will be collected: samples for the assessment of oral/fecal microbiota, breath samples, BMI, disease duration, clinical phenotype and ocular, articular or mucocutaneous involvement and information about eating habits. Patients in the treatment arm will assume 5 g per day of inulin in addition to their ordinary diet and in a randomized order. The 5 g dose was chosen after considering the amounts of prebiotics that would be sufficient to induce positive and significant changes in the gut microbiota, but low enough to avoid adverse effects and minimize gastrointestinal discomfort (Bouhnik et al., 1999; Kolida et al., 2007).

All data obtained, will be analyzed with innovative AI methods, in order to evaluate the conditions of eubiosis/dysbiosis and to identify potential microbial and metabolic markers linked to BD, to eating habits of patients and to a soluble fiber dietary supplement administration.

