### Data analysis

2.8

Data collected by investigators will include volatilome, oral/fecal microbiota, body mass index (BMI), disease duration, clinical phenotype and ocular, articular or mucocutaneous involvement.

The microbiota can be characterized in three different ways: alpha diversity metrics, relative abundance of phylotypes for each specimen and community state types (CST). Alpha diversity metrics, which represent the variety and richness of organisms in a specimen, and relative abundance of microbes will be analyzed through supervised machine learning algorithms as Random Forest or XGBoost classifiers. Supervised machine learning is a category of machine learning where the algorithm is trained on a labeled dataset, which means that each example in the training data is associated with the correct output or target. The algorithm learns to make predictions or decisions based on input data by generalizing from the labeled examples it has seen during training. Moreover, the XAI algorithm “SHapley Additive exPlanations” (SHAP) will be used to detect for each patient, which features are more important for the ML algorithm in its classification (Bellantuono et al., 2023; Novielli et al., 2023). SHAP is an algorithm used in machine learning to explain the predictions made by complex models, particularly for models like XGBoost, Random Forest, neural networks, and others. It provides interpretable explanations for individual predictions, helping users understand why a particular prediction was made. The third characterization, i.e., CST, which groups samples according to the composition of the microbiota, will be analyzed through the application of complex networks (CN). This mathematical method, also known as complex systems or complex networks theory, is a branch of network science that studies systems characterized by a large number of interconnected components or nodes, and the patterns and properties that emerge from these connections. In our case, interactions between microbiome and its host are complex phenomena, and to better understand this kind of complex interactions and to map microbiome behavior is of fundamental importance to have the possibility to model these interactions through CN. Modules of this complex biological network are key organizational elements for the network itself. To detect modular organizational structures of a complex network, community detection unsupervised algorithms will be used.

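### Features that predict outcome, or that separate the arms at month 3, are read as markers of response to inulin, although no stated analysis compares a marker's effect between the randomised arms

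*Protocol article*

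**What the plan says.** The design is a two-arm randomised comparison: "patients in the control arm will keep on assuming the standard therapy while patients in the treatment arm will assume soluble inulin-type fructans" on top of standard therapy. Allocation is one to one: "The fiber dietary supplement will be administered randomly to half of the study patients, in open-label mode". There are two measurement times: "At the starting of study and 3 months later, for each patient, the following samples and data will be collected".

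The Introduction describes a relapsing disease ("The most recurring signs of this disease are relapsing genital and oral aphthae"), and Study population admits patients who are active or in remission on the BDCAF.

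The aims at the end of the Introduction concern prediction of outcome. Aim (iii) seeks taxa and metabolic markers that predict clinical outcomes. Aim (iv) seeks markers that, "for each patient, contribute to the prediction of his/her clinical outcome (personalized medicine"). Outcome measure makes the primary analysis a data-driven separation of the two arms at 3 months from microbiota and volatilome profiles, and treats local feature importance as insight into each patient's metabolic response to treatment. Data analysis says SHAP "will be used to detect for each patient, which features are more important for the ML algorithm in its classification".

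Anticipated results then says that "this study will evaluate for the first time with multivariate models if microbiome and breath modulation through the diet can improve disease activity". The next sentence says this analysis could "enable us to find valuable markers to identify responders and non responders, allowing treatment optimization and a personalized therapeutic approach". The word could stands in the text just before the quoted words.

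**The concern.** A prognostic marker says who does well at 3 months whatever the treatment. A responder marker says for whom inulin makes a difference, so it is a statement about treatment effect. Only the second can guide who should receive the supplement. The article states analyses that give the first, or that identify arm membership, and attaches to them an interpretation that needs the second.

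The distinction matters here because activity fluctuates and each patient contributes a single before-after change under one condition. That change mixes any inulin effect with natural course and regression to the mean. A feature that tracks baseline activity, such as ESR, CRP or a taxon linked to inflammation, can predict improvement when inulin does nothing. The cross-validation described in the article would not reveal this, since a prognostic marker validates just as well as a responder marker.

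**Working it through.** **1. What each stated analysis can show.**

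- *Outcome prediction, aims (iii) and (iv).* The target is clinical status. No arm restriction and no between-arm contrast is stated. The result is prognostic.
- *Primary classifier, Outcome measure.* The label is arm and the features are month-3 profiles. A high local SHAP value shows why a patient's profile looks like that of an inulin taker, not whether that patient improved clinically. Month-3 features also arise after treatment, so they cannot be used to choose patients before it.
- *Multivariate models, Anticipated results.* These ask whether modulation through diet improves disease activity. No marker-by-arm contrast is described.

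**2. Completers.** The article gives no figure for responder analyses, so the number available comes from its sample size section (α = 0.05, power 0.80, effect size 0.80, 26 patients, 20% dropout, 35 per group). Reading 26 as per group, a two-sided two-sample t-test needs 25.5, so 26: reproduced. Allowing for dropout, 26/0.8 = 32.5, so 33; the stated 35 is slightly more generous. Completers: 35 × 0.8 = 28 per arm, 56 in all.

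**3. Apparent response with no inulin effect.** Assumptions, not document figures: activity score normal with equal SD at both visits, test-retest correlation ρ over 3 months, improvement defined as at least 0.5 SD, and a marker correlated 0.6 with baseline activity.

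- SD of change = √(2(1 − ρ))
- P(improve by at least 0.5 SD) = Φ(−0.5 / SD of change)
- Correlation of baseline with change = −√((1 − ρ)/2)
- Correlation of the marker with change = 0.6 × the line above, if the marker is linked to change only through baseline activity

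| ρ | SD of change | P(improve) | baseline–change | marker–change |
|---|---|---|---|---|
| 0.3 | 1.183 | 0.336 | −0.592 | −0.355 |
| 0.5 | 1.000 | 0.309 | −0.500 | −0.300 |
| 0.7 | 0.775 | 0.259 | −0.387 | −0.232 |

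A separate simulation under the same null gave 32%, 29% and 21% improving for ρ = 0.4, 0.6 and 0.8.

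**4. One-arm search against a two-arm contrast.** In 4,000 simulated trials with 28 completers per arm, no inulin effect and a purely prognostic marker (assumed slope 0.5 SD per SD, residual SD 1), testing the marker in the inulin arm alone was significant in 69%. The marker-by-arm term fitted in both arms together was significant in 5%, its nominal rate.

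**5. Precision of the two-arm contrast.** With marker and residual SD of 1, the standard error of the slope difference is about √(2/28) = 0.267. The difference detectable with 80% power is (1.96 + 0.84) × 0.267 = 0.75 SD per SD. The inulin effect would have to differ by 0.75 × 2 = 1.5 SD between patients one SD above and one SD below the marker mean. For a marker split 50/50 the figure is 2.80 × √(4/14) = 1.5 SD.

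**The case against.** The strongest reply is that the responder sentence is a hedged hope in the Discussion, not a specified analysis, and that a responder definition or an interaction term may sit in a fuller plan that is not shown. Their absence from the article is indeed no fault. The reply does not dispose of the point, which rests on what the article states: aims framed as outcome prediction, a classifier of arm, and an interpretation framed as treatment response. The same interpretation appears in Outcome measure, outside the Discussion.

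A reader might infer more: that the control arm goes unused, and that spontaneous improvement will be labelled as response to inulin. The documents do not support that. The trial has a concurrent randomised control arm measured at both visits, the primary analysis compares the arms, and nothing says the responder search is confined to inulin patients. Could be mislabelled is as far as the text goes.

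Three further limits stand. The aims and the Data analysis section do not mention responders; that word occurs only in Anticipated results. The article calls the aphthae relapsing but does not say that they remit without a change of treatment. It also refers there to patients under treatment, so responder might be meant partly in relation to background therapy; even so, the sentence follows directly on a question about modulation through diet.

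**Conclusion.** The point holds as a mismatch between the stated analyses and the interpretation placed on them. Neither outcome prediction nor classification of arm from month-3 profiles can separate response to inulin from natural course in a relapsing disease seen at two visits. Under no inulin effect, about 26% to 34% of patients would improve by at least 0.5 SD for assumed correlations of 0.7 down to 0.3.

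These percentages illustrate the mechanism and are not estimates for this trial. The correlations, the threshold, the marker correlation and the prognostic slope are all assumed, and normality is doubtful for an activity score in a cohort mixing active and remitted disease. The 69% in the simulation applies only if markers were sought in the inulin arm alone, which the article does not say. The conclusion itself follows from the design and the stated aims and does not depend on these values.

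**What to change.** 1. In aim (iv) and Anticipated results, describe features that predict 3-month outcome as prognostic. In Outcome measure, describe local feature importance from the arm classifier as explaining the classification, not as an individual's response to treatment.
2. Reserve responder marker for a baseline feature whose relation to 3-month BDCAF, adjusted for baseline BDCAF, differs between the randomised arms. Estimate this with a marker-by-arm term in one model fitted to both arms. Carrying a model built in the inulin arm over to controls is not an adequate substitute: fitted to about 28 patients, it would tend to perform worse elsewhere through overfitting alone, and that loss could pass for a differential effect.
3. Label this analysis exploratory and drop treatment optimisation as an expected result of this trial.

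The cost is wording plus one analysis of planned data: BDCAF is a listed outcome and classifies patients at entry. The downside is a weaker claim, since with about 56 completers only very large differences in effect could be detected reliably.

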### Outcome measure

2.5

In the initial phase of our study, our primary focus lies in a data-driven analysis designed to distinguish, at the 3-month period, two distinct patient groups based on microbiota and volatilome profiles. The first group undergoes traditional treatment with soluble fiber intake (inulin), while the other receives only traditional treatment. This outcome is propelled by the application of Explainable Artificial Intelligence (XAI) techniques, aiming to uncover the pivotal features contributing to the differentiation between the two groups. Our investigation extends to understanding the global and local importance of these features, providing insights into the personalized metabolic responses to treatment.

The outcome measures considered are summarized in Table 1. Integrating these biological and clinical parameters using a data-driven approach, our objective is to paint a comprehensive picture of the personalized metabolic markers associated with Behçet’s disease. This dual-phase evaluation not only enriches our understanding of microbiome and metabolome nexus with the disease but also lays the groundwork for targeted interventions and more detailed treatment strategies.

**Table 1 tab1:** Biological and clinical outcome measures considered in the presented protocol study.

Biological outcome measures	Erythrocyte sedimentation rate (ESR)
	C-reactive protein (CRP)
Clinical outcome measures	Behçet’s Disease Current Activity Form (BDCAF) – measure of disease activity
	Krause Total Severity Score – measure of disease severity
	Short-form (SF)-36 quality of life (QoL) scale – measure of disease QoL

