### Comprehensive methodology for data challenges

2.9

To ensure a robust evaluation of our models, we will implement a cross-validation strategy. Cross-validation involves partitioning the dataset into subsets, training the model on some of these subsets, and testing it on the remaining subset. This process will be repeated multiple times, and the performance metrics will be averaged. This approach ensures that our models generalize well and helps prevent overfitting.

To handle the possible presence of missing values, we will adopt a two-fold approach:

*Variable Selection*: Variables with a relatively low percentage of missing values (below a defined threshold, e.g., 30%) will be considered to maintain data quality.*Imputation Techniques*: For variables exceeding the threshold, established imputation techniques will be employed. Additionally, we will use imputation methods such as replacing missing values with the mean or maximum of the respective variable. Importantly, these techniques will be applied separately to the training and testing datasets to prevent data leakage and ensure model generalization to unseen data.

We would also like to highlight the utility of the XGBoost algorithm, which inherently handles missing values in tree algorithms by learning branch directions during training.

To handle the potential limitation in the number of available patterns compared to the number of features considered, which could lead to overfitting, we will address the issue through the implementation of two robust techniques: data augmentation and feature reduction.

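### Clustering SHAP explanations of a supervised model can show patient subgroups where none exist, so the subgroups anticipated in section 3.2 need held-out explanations and a label-permutation reference

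*Protocol article*

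**What the plan says.** The protocol article describes more than one route to groups of patients or samples.

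- **Label-free routes.** Aim (ii) in the Introduction is to "identify, through cluster analysis methods of metabolites, different groups of patients affected by BD". Section 2.8 (Data analysis) adds a network analysis of community state types: "To detect modular organizational structures of a complex network, community detection unsupervised algorithms will be used".
- **Route through a supervised model.** Section 3.2 (Anticipated results) says: "By incorporating local explanation embeddings and an unsupervised clustering method, we could anticipate the identification of distinct subgroups among subjects". The sentence after it ties this to personalised interventions.

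Section 2.8 shows what the local explanations are. Diversity metrics and relative abundances "will be analyzed through supervised machine learning algorithms as Random Forest or XGBoost classifiers", and SHAP "will be used to detect for each patient, which features are more important for the ML algorithm in its classification". Section 2.5 (Outcome measure) gives the main classification task, which is "to distinguish, at the 3-month period, two distinct patient groups based on microbiota and volatilome profiles", meaning inulin plus standard treatment against standard treatment alone. The aims also allow clinical outcomes as labels, since they seek "metabolic markers that majorly contribute to the prediction of different clinical outcomes".

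The safeguard against overfitting is in section 2.9: "To ensure a robust evaluation of our models, we will implement a cross-validation strategy". It is described as repeated training and testing with averaged performance measures. The article does not say that it extends to the SHAP values that are clustered.

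**The concern.** SHAP values are not measurements on the patient. They are a fitted model's account of why it moved that patient towards one label or the other. A flexible tree model fitted to 70 patients with many features separates the two labels perfectly in the data it was trained on, even if no feature carries information. Its in-sample SHAP values then differ systematically by label, and a clustering algorithm finds that difference.

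The usual safeguard does not help. A cluster-validity check on the SHAP embedding asks whether the SHAP values form a single cloud. It does not ask whether the patients form subgroups. The check can pass for reasons that lie in the model alone.

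At stake is a claim that distinct patient subgroups exist, which the article links to personalised treatment. If the label is the randomised arm, such subgroups could largely restate who received inulin.

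**Working it through.** **1. Scale of the problem.** The article gives no figure for the clustering step, so only its sample size can be reproduced. Section 2.4 uses α = 0.05, power 0.80 and effect size 0.80. The normal approximation gives 2 × (1.960 + 0.842)² / 0.80² = 24.5, so 25 per group. The t-test version gives 25.52, so 26, as stated. Allowing for 20% dropout, 26 / 0.80 = 32.5, so 33 against the stated 35. The simulations use the stated 35 per group, 70 in total.

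**2. Assumptions, none fixed by the article.** Independent Gaussian features with no relation to the label, and a balanced 35/35 label. The models are XGBoost (depth 3, 100 rounds), a random forest and boosted stumps. Clustering is k-means with k = 2. SHAP values are taken either in-sample or from 5-fold held-out fits.

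**3. Measures.**
- Silhouette: the mean over patients of (b − a) / max(a, b), where a is the mean distance to the patient's own cluster and b the mean distance to the other cluster.
- Label agreement: max(m, 1 − m), where m is the share of patients whose cluster number equals the label. Because the better matching is taken, chance is above one half: 0.5 + √(2/π) × 0.5/√70 = 0.5 + 0.798 × 0.0598 = 0.548, about 55%.

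**4. Results under pure noise, n = 70** (means over 40 runs per setting for XGBoost and random forest, 60 for stumps; each cell is silhouette / label agreement)

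| Model, features | Raw features | In-sample SHAP | Held-out SHAP |
|---|---|---|---|
| XGBoost, 50 | 0.03 / 0.55 | 0.25 / 0.88 | 0.17 / 0.61 |
| XGBoost, 200 | 0.01 / 0.54 | 0.27 / 0.90 | 0.15 / 0.60 |
| Random forest, 50 | 0.03 / 0.55 | 0.23 / 0.82 | 0.15 / 0.62 |
| Random forest, 200 | 0.01 / 0.54 | 0.18 / 0.94 | 0.08 / 0.63 |
| Stumps, 50 | 0.03 / 0.55 | 0.22 / 0.67 | 0.15 / 0.60 |
| Stumps, 200 | 0.01 / 0.55 | 0.20 / 0.73 | 0.13 / 0.61 |

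In-sample AUC was 1.00 and held-out AUC 0.48-0.52, so the models had learned nothing real. A further XGBoost run with 44 and 200 features gave a silhouette of 0.22-0.25 and agreement of 80-85% in-sample, 0.15-0.16 and 61-62% held-out, and 0.01-0.03 and 55% on raw features. The verdict uses these more cautious figures.

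**5. Would a cluster-validity check catch it?** An illustrative check declares structure when the silhouette exceeds all 19 covariance-matched Gaussian references (nominal rate 1/20 = 5%). With XGBoost under pure noise, it declared structure as follows:

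| Patients, features | In-sample SHAP | Held-out SHAP | Raw features | Reference from label-permuted reruns |
|---|---|---|---|---|
| 70, 250 | 83% | 33% | 0% | 7% |
| 56, 250 | 83% | 25% | 0% | 10% |
| 70, 44 | 72% | 37% | 0% | 5% |

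(56 = 70 × 0.80.) The last column rests on 54 to 60 datasets each. With 60 datasets the standard error at 5% is √(0.05 × 0.95 / 60) = 2.8 percentage points, so 5-10% is compatible with the nominal rate.

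**6. A real arm effect but no subgroups.** Five features were shifted equally for every treated patient (XGBoost, 50 and 200 features, 40 runs per setting). In-sample SHAP clusters matched the arm in 84-85% of patients at a shift of 0.8 SD and in 90-92% at 1.2 SD.

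**The case against.** Four points against the concern have weight.

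- **The sentence is hedged and sits in the Discussion.** Sections 2.8 and 2.9 contain no step that clusters explanations. This stands: the article anticipates subgroups and does not promise them. It still names the method and its intended use.
- **The stated aim for patient groups clusters metabolites.** This also stands. A reader might infer that aim (ii) depends on SHAP clustering, but its text says otherwise.
- **Cross-validation is planned.** It would make held-out SHAP values available, and it would show an AUC near 0.5 before anyone interpreted the explanations. This stands in part. The article applies cross-validation to performance and states no rule that a poor model is not explained. Held-out values remove most of the label echo but not the false separation. The noise rates above are not restricted to models that looked predictive.
- **The rest is detail for a fuller document.** Choices such as the number of clusters and resampling settings are indeed no finding. The mismatch is different in kind: separated attributions do not establish subgroups of patients, and more detail on an ordinary validity check would not change that.

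A reader might also infer that the trial would report false subgroups almost for certain, or that any it finds would be artefacts of the label. The documents do not support this. They do not say whether the SHAP values are in-sample, and noise simulations cannot show that subgroups found with real signal are false. Nor is it evidence that k-means with k = 2 always returns two groups, since it does so on any data, including the raw features.

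**Conclusion.** The concern holds in conditional form. If the subgroups anticipated in section 3.2 come from clustering SHAP values of a supervised model, apparent subgroups can arise with none present. With in-sample values and XGBoost at n = 70, the clusters restate a meaningless label in about 80-85% of patients, against 55% by chance. With held-out values agreement falls to about 61-62%, but the silhouette of about 0.15 is still clearly above the 0.01-0.03 of the raw data.

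The sizes rest on 44 to 200 independent Gaussian features, two clusters, untuned models and none of the feature reduction planned in section 2.9. Real microbiota data are correlated and compositional, so the figures will differ. The mechanism does not depend on the exact settings: it appeared with all three tree models, with a weaker label echo for boosted stumps. This is a cheap improvement to an exploratory step, and it does not undermine aim (ii).

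**What to change.** In section 3.2, and in section 2.8 if the step is kept as an analysis:

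1. Keep the label-free metabolite clustering of aim (ii) as the basis for claiming that patient groups exist.
2. If SHAP embeddings are clustered, use held-out SHAP values only.
3. Compare the chosen cluster index with its distribution when the labels are permuted and the whole sequence of model, SHAP and clustering is rerun. Claim structure only if the index exceeds that distribution.
4. Cross-tabulate the clusters with the training label, and do not present clusters that restate it (for example the randomised arm) as new subgroups. Step 3 does not cover this, because a uniform arm effect could pass the permutation comparison without any subgroup within arms.
5. Otherwise report that no subgroups were shown.

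The cost is a few sentences and the computing time for a few hundred reruns on 70 patients. The downside is that the study may have to report that no subgroups were shown.
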